#### Secondary research aim

The secondary research aim is to explore the dose effects of 3 different weekly volumes of HIFT on cardiorespiratory fitness, body composition, resting blood pressure (BP), and resting heart rate (HR) after a 12-week training program.

#### Tertiary research aim

The tertiary research aim is to investigate the subjective responses of “exercise enjoyment” and “intention to continue” after a 12-week HIFT training program of 3 different weekly volumes.

### Trial design {8}

The present study is a parallel-group, three-arm, exploratory, randomized, dose-response clinical trial. Randomization is at a 1:1:1 allocation ratio for the three arms.

## Methods

### Study setting {9}

The intervention and measurements will take place in Western Colorado University’s (WCU) High Altitude Performance (HAP) Laboratory and Gunnison Valley Health Hospital (GVH) in Gunnison, CO, USA.

### Eligibility criteria {10}

Participants will be included on the condition that they (1) are between the ages of 35 and 65 years old; (2) self-report physical inactivity (less than 30 min per day, 3 times per week, for 3 months); (3) possess at least 3 of the 5 risk factors defining MetS (waist circumference ≥ 102 cm (men), ≥ 88 cm (women), resting BP ≥ 130/85, HDL-C ≤ 40 mg/dl (men) ≤ 50 mg/dl (women), fasting TG ≥ 150 mg/dl, and fasting blood glucose (FBG) ≥ 100 mg/dl); (4) have no diagnosis of or taking medication for heart, lung, kidney, liver, or neurological diseases; and (5) have no medical or orthopedic conditions that prevent them from performing exercises. All exercise and measurements performed in the HAP Lab will be supervised and executed by trained exercise scientists. All measurements performed at GVH will be executed by the technicians at the hospital.

To assess participant eligibility, participants will visit the HAP Lab in a fasted state and complete the initial screening. Participants will be measured for resting BP and HR, resting blood oxygen saturation SaO_2_, height, weight, waist circumference, and abdominal height [8, 69]. Next, 40 μL of capillary blood will be collected via fingerprick and analyzed for TC, LDL-C, HDL-C, TG, and FBG with the Cholestech LDX Analyzer [Abbott Diagnostics, Abbott Park, IL]. TG/HDL ratio will be calculated. Participants will then complete a physical activity and diet questionnaire (Full Block Questionnaire, NutritionQuest, 2014) [70, 71], and all included participants will be asked to maintain their self-reported diet throughout the entire study.

### Who will take informed consent? {26a}

All participants will undergo a process of informed consent and discussion with the principal investigator and complete a health history questionnaire prior to eligibility screening. Written information concerning the needs, benefits, and risks of the trial will be delivered, and a verbal explanation will be given. The discussion will include a check of understanding regarding participation and assurance that the participant accepts or does not accept participation. Participants will also be informed that the allocation of treatment will be random regardless of any personal preference they may have.

### Additional consent provisions for collection and use of participant data and biological specimens {26b}

Biological specimens will not be stored for future use and therefore will not be available for ancillary studies. Future use for all other trial data is included in the original informed consent.

### Intervention

#### Explanation for the choice of comparators {6b}

According to the literature, the investigated dose of HIFT exercise is 3 times per week [55, 58, 60–62]. This dose is in line with the global physical activity guidelines [22]. However, HIIT and resistance exercise, two components of HIFT, have shown health and fitness benefits as little as 2 times per week [64–67]. No studies have investigated the health benefits of HIFT less than 3 times per week. The current study aims to investigate the dose-response effects of differing weekly volumes of HIFT. This choice of comparators seeks to elucidate the minimum amount necessary to elicit clinically meaningful benefits. A non-exercise control group will not be included as to not withhold the benefits of exercise from the study population [72, 73].

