**Discussion:**

The findings of this research will provide evidence on the minimal dose of HIFT per week to see clinically meaningful improvements in the risk factors of MetS, as well as whether this modality is likely to mitigate the barriers to exercise. If an effective dose of HIFT per week is determined and if this modality is perceived positively, it may provide exercise specialists and health care providers a tool to prevent and treat MetS.

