#### Sample size {14}

The sample size was projected with a change in ApoB as the main outcome variable between HIFT1 and HIFT3. Power calculations (IBM SPSS v25 Armond, NY) assumed a 1:1 equal allocation between HIFT1 and HIFT3. The baseline mean and standard deviations from a previous study [97] and pilot studies for ApoB were ~ 129 ± 25 mg/dL in sedentary adults with elevated cardiometabolic risk. Collectively, using these data, we consider a 15% reduction in ApoB to be clinically meaningful within the HIFT3 group [98]. Assuming a power of 0.90, *α* = 0.05, and an effect size of *d* = 0.80, a paired samples one-tailed *t*-test sample size calculation revealed a sample size of 60 subjects (20 per group) will establish the superiority of HIFT3 versus HIFT1 for pre- to post-differences in the primary outcome ApoB. With an estimated 5% dropout rate, we will recruit 22 subjects/group to obtain the necessary sample size of 60. Therefore, a total of 60 men and women who meet the previously stated inclusion criteria will be recruited and randomized post-baseline assessments into one of the three intervention groups. Data will be collected in cohorts of 12, randomized into intervention groups. This will continue until 20 participants per intervention group have completed the study. This will accommodate dropout within cohorts.

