#### Recruitment {15}

Participants will be recruited via advertisement flyers posted in the communities of Gunnison County, social media, word of mouth, employee email lists of WCU and GVH, local newspaper and magazine ads, churches, and through physician referral among the Gunnison County health care providers. To account for the logistical capacity of data collection, participants will be recruited in cohorts of 12 (randomized into intervention groups) where each cohort will complete the entire study before the next cohort begins. This will continue until 20 participants per intervention group have completed data collection.

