## Statistical methods

### Statistical methods for primary and secondary outcomes {20a}

Only data from participants who complete ≥ 80% of total exercise intervention and with no noticeable change in eating (statistically different energy consumption and macronutrient distribution) and physical activity habits will be included [97, 99, 100]. All data will be analyzed using the Statistical Package for the Social Sciences (IBM SPSS v25, Armond, NY). Descriptive data if normal will be presented as mean ± SD, or median and interquartile range if not normal; the significance level of all comparative data will be set as *p* ≤ .05, and normality will be assessed using a Kolmogorov-Smirnov test. If normality exists, parametric tests will be used, if normality does not exist, non-parametric tests will be used. Effect sizes (ES) and confidence intervals (CI) will be calculated on the results of all dependent variables. Paired *t*-tests will be used to evaluate the significant differences between pre- and post-measures of both primary and secondary physiological outcomes within each group. A one-way ANOVA will be used to compare the primary and secondary outcomes pre-post mean change between the three groups. When indicated by a significant *F* value, post hoc analysis will be determined using the Bonferroni adjustment for multiple comparisons. The median, mode, and interquartile ranges of the IFIS and PACES data will be calculated for each of the three groups. Should missing data in outcomes occur, a linear-mixed model will be conducted instead of ANOVA as this test accounts for missing data.

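### The protocol promises a minimum effective weekly dose, but with no non-exercise arm its only tests of a single dose are uncontrolled pre-post comparisons against zero

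*Protocol article*

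**What the plan says.** Three places in the protocol article describe what the trial will deliver.

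- Explanation for the choice of comparators {6b}: "This choice of comparators seeks to elucidate the minimum amount necessary to elicit clinically meaningful benefits".
- Abstract, Discussion paragraph: the findings will "provide evidence on the minimal dose of HIFT per week to see clinically meaningful improvements in the risk factors of MetS".
- The last paragraph of the main Discussion repeats the minimal-dose aim and expects the results to feed into exercise programming guidelines for metabolic syndrome.

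The same section {6b} rules out an untreated comparator and gives the reason: "A non-exercise control group will not be included as to not withhold the benefits of exercise from the study population".

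Statistical methods {20a} plans two kinds of test at p ≤ .05. A one-way ANOVA compares mean change between the three arms, with Bonferroni post hoc tests. Paired t-tests are to "evaluate the significant differences between pre- and post-measures of both primary and secondary physiological outcomes within each group". Effect sizes and confidence intervals are to be calculated for all dependent variables, but they are not set against any threshold.

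A meaningful change is named only in Sample size {14}: "we consider a 15% reduction in ApoB to be clinically meaningful within the HIFT3 group". No analysis refers to it.

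Participant timeline {13} and Intervention description {11a} place baseline testing before a three-week familiarisation period of two sessions a week. Every participant attends it before randomisation.

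**The concern.** Whether a given dose produces a clinically meaningful benefit is a question about that dose against no exercise. The randomised comparison cannot answer it: the ANOVA is silent on whether one session a week does anything. The only planned tests that appear to answer it are the within-arm paired t-tests, and these have two weaknesses for the purpose.

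1. They are uncontrolled. Anything that moves ApoB in all arms is counted as an effect of the allocated dose. One such exposure is built into the schedule: the shared training between baseline and randomisation.
2. They test against zero. A significant result does not show that the change is as large as the protocol's own meaningful figure.

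Suppose all arms fall and the ANOVA is not significant. A reader of the stated aims could conclude that one session a week is enough. The same data would fit a change unrelated to the allocated dose, or a real dose difference that 20 per arm failed to detect. Since the results are meant to inform guidelines, this conclusion needs to be one the design can bear.

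**Working it through.** **Inputs from the protocol.** Sample size {14}: ApoB about 129 ± 25 mg/dL, 20 completers per arm, meaningful reduction 15% (stated for HIFT3). Statistical methods {20a}: p ≤ .05, sidedness not stated. The 20 per arm is taken as given; how it was derived is a separate question.

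**Assumptions.** The protocol gives no SD of change, so I use pre-post correlations r of 0.5, 0.7 and 0.8. It gives no shared change, so I show 0%, 5%, 7.5% and 10%.

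**The meaningful figure in mg/dL.** 0.15 × 129 = 19.35.

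**Shared training in the HIFT1 change.** Run-in: 3 weeks × 2 = 6 sessions. Allocated: 12 weeks × 1 = 12. So 6 of 18 supervised sessions (33%) between HIFT1's two measurements are not the allocated dose. For HIFT2 it is 6 of 30 (20%) and for HIFT3 6 of 42 (14%). The run-in is lighter: week 1 is movement screening and technique, week 2 half and week 3 three quarters of phase 1 volume.

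**Smallest significant within-arm fall.** SD of change = 25 × √(2(1 − r)). Critical fall = t × SD / √20, with two-sided t on 19 df = 2.093.

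| r | SD of change | Critical fall, mg/dL | % of 129 | Share of 19.35 |
|---|---|---|---|---|
| 0.5 | 25.0 | 11.7 | 9.1% | 60% |
| 0.7 | 19.4 | 9.1 | 7.0% | 47% |
| 0.8 | 15.8 | 7.4 | 5.7% | 38% |

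The two-sided critical fall drops below half of the target only when r exceeds about 0.66. A one-sided test, the kind named in the sample-size section, gives 9.67, 7.49 and 6.11 mg/dL, or 50%, 39% and 32% of the target.

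**Chance that HIFT1 shows a significant fall when the arms share a change and dose has no effect.** Noncentral t, two-sided test, n = 20, noncentrality = shared fall / (SD / √20). For a 5% fall (0.05 × 129 = 6.45 mg/dL) at r = 0.7: 6.45 / (19.36 / 4.472) = 1.49.

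| Shared fall | r = 0.5 | r = 0.7 | r = 0.8 |
|---|---|---|---|
| 0% | 2.5% | 2.5% | 2.5% |
| 5% (6.45 mg/dL) | 19% | 29% | 41% |
| 7.5% (9.675 mg/dL) | 38% | 56% | 74% |
| 10% (12.9 mg/dL) | 59% | 81% | 93% |

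**The same event with a non-significant ANOVA.** By simulation of three arms of 20 with a 5% shared fall, HIFT1 is significant and the ANOVA is not in about 17.5%, 27% and 38.5% of trials for r = 0.5, 0.7 and 0.8.

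**Precision of the comparison the design does support.** The 95% half-width for HIFT1 minus HIFT3 is 2.024 × SD × √(2/20), with t on 38 df. This gives 16.0, 12.4 and 10.1 mg/dL, or 83%, 64% and 52% of 19.35. Even with identical observed changes in the two arms, only a loss larger than that could be excluded.

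**The case against.** **The protocol states no rule that turns a paired test into a minimum dose.** This is correct. A reader might infer that a significant paired test with a non-significant ANOVA is the planned criterion for declaring one session sufficient. Nothing in the article says so, and a classification rule could sit in an analysis plan that is not shown. What stands without any rule is that the promised conclusion goes beyond what the randomised contrasts can show, and no analysis plan can supply the missing comparator.

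**The formal aims fit the design.** The hypothesis, the primary aim and the sample-size contrast (HIFT3 versus HIFT1) are all dose against dose. The trial calls itself exploratory and gives a reason for having no untreated arm. This supports the remedy: the aims are sound, and it is the minimal-dose wording in {6b}, the abstract and the Discussion that goes further.

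**Other sources of shared change are partly handled.** A reader might blame season, diet awareness or selection on abnormal values. ApoB is not an eligibility criterion, and screening uses a separate capillary sample from the later baseline venous draw, so settling after selection is reduced and at most indirect. Cohorts run in sequence ("each cohort will complete the entire study before the next cohort begins"), so they start at different times of year and seasonal effects tend to average out. Diet and activity are to be kept constant, are checked by repeated questionnaires, and participants whose habits change are excluded from the main analysis. None of these is shown to be a material problem. The shared run-in is the one clearly documented exposure.

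**The size depends on assumptions.** This also stands. The 5% fall is illustrative, and with no shared change the false-positive rate for a fall is 2.5%.

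**Conclusion.** The concern holds as a mismatch between conclusion and design. Without a non-exercise arm the trial can say how the doses differ, but not which dose is the least that works. The only planned tests of a single dose are uncontrolled, include six shared sessions held after baseline, and are not tied to the 15% figure, which the protocol itself states for HIFT3 only.

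In size, a within-arm ApoB fall of 60%, 47% or 38% of that figure would already be significant (two-sided, 20 per arm, r = 0.5, 0.7, 0.8). A reader might go further and say that any change under half the meaningful size will pass. That needs r above about 0.66 or a one-sided test, and the protocol gives neither the SD of change nor the sidedness of the analysis tests. Under an assumed 5% shared fall, HIFT1 would show a significant fall in 19% to 41% of trials. These figures show how exposed the test is to shared change; they do not predict that such a change will occur.

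**What to change.** 1. In the abstract's Discussion paragraph, section {6b} and the closing paragraph of the main Discussion, limit the conclusion to differences between doses, and say that effectiveness against no exercise cannot be concluded.
2. In Statistical methods {20a}, label the within-arm paired tests descriptive. Report each arm's mean ApoB change with its 95% confidence interval beside the 15% figure, described as uncontrolled and as including the run-in.
3. State that a lower dose will be called sufficient only if the 95% confidence interval for its difference from HIFT3 excludes a loss of benefit that the sponsor fixes in advance.
4. State that a non-significant ANOVA is not evidence that the doses are equal.

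These are wording changes to the protocol and analysis text; no extra arm, visit or participant is needed. The price is a more modest conclusion. With half-widths of about 10 to 16 mg/dL for HIFT1 against HIFT3, the minimum dose may remain undetermined at 20 per arm, and the report should then say so.

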#### Intervention description {11a}

For 3 weeks prior to the 12 weeks of training, participants will undergo exercise familiarization 2 days/week. Participants will then be randomized into 1 of 3 exercise dose groups (HIFT1, 1 session per week; HIFT2, 2 sessions per week; HIFT3, 3 sessions per week). Then, 12 weeks of supervised training will commence consisting of three 4-week phases, where intensity, duration of exercise, and recovery time are progressed each phase.

##### Three-week adaptive period

Twice a week for 3 weeks, participants will visit the HAP Lab to learn proper techniques and familiarize themselves with HIFT exercises. Week 1 will consist of a movement screening to assess the participant’s capabilities of multi-planar, functional movements (squat, hinge, lunge, push, pull, press, and rotation) [74, 75]. Corrections and modifications will be advised to participants, then movements will be trained to ensure proper, safe exercise. If proper movement is not attained within week 1, this familiarization will be extended until satisfaction before progression. Week 2 will consist of learning a structured HIFT routine using minimal load at half of phase 1 volume (see Fig. 1). Week 3 will consist of HIFT rehearsal bouts at ¾ of phase 1 volume (see Fig. 1). Load or resistance will be added to the exercise on an individual basis, aiming for a target perceived effort of ≥ 7 on the Borg Session RPE CR10 Scale (sRPE) [76–79]. Examples of load or resistance are bodyweight, suspension bands, medicine balls, kettlebells, dumbbells, elastic bands, and stability balls. Additionally, participants will be familiarized with the aerobic intensity target (HR ± 5 beats of second ventilatory threshold (VT2)) for each set within the HIFT session. To quantify these intensity targets, HR and sRPE will be measured immediately after each set. Participants will be familiarized with this data collection procedure and intensity target during week 3 [79]. Participants will then be randomized and scheduled for their 12 weeks of training based on their allocated dose (HIFT1, HIFT2, or HIFT3).

**Fig. 1 Fig1:**
[figure not shown]
HIFT session example (phase 1). As many rounds as possible (AMRAP)

##### Twelve-week HIFT training period

Participants will perform their allocated HIFT sessions. All sessions will use asynchronous music playing and be supervised by a Certified Medical Exercise Specialist (CMES) or specifically trained exercise science undergraduate and graduate students when the CMES is unable to attend. These personnel will facilitate exercise instruction, duration and effort monitoring, and data collection and provide standardized encouragement to participants. HIFT sessions will be scheduled on Monday, Wednesday, and Friday in the morning and during the lunch hour, where participants can attend according to their personal schedules and allocated dose group. HIFT session attendance will be organized to ensure between 2 and 5 people at each scheduled time. The training protocol will be divided into three 4-week phases where exercise is progressed in both intensity and volume during each phase, with the last week of each phase being digressed to 60–70% of the volume [80, 81].

Progression of volume will follow the characteristics in Table 1. Progression of load will be individualized for each exercise using the session RPE (sRPE) method, with a target sRPE ≥ 7 (Borg CR10) after each set within the workout [76–79]. The aerobic intensity target (HR ± 5 beats of VT2) will remain throughout. To quantify these intensity targets, HR and sRPE will be measured immediately after each set and recorded by exercise personnel. If a participant’s sRPE falls below 7 or HR falls below the established target, the load will be incrementally increased upon the next training session. Examples of load progression are adding weight or modifying the position of the body to increase resistance or adding elements of velocity to the movement. This personalized method ensures that load/effort is progressed based on each individual’s rate of development and is easily translated into a real-life training session. It also affords the flexibility to be applied to a wide range of exercises and precludes the need for specific maximal strength assessment such as 1RM for subsequent prescription of load percentages.

**Table 1 Tab1:** Progression characteristics of the 12-week training period

Training parameters	Phase 1		Phase 2		Phase 3	
	Weeks 1–3	Week 4	Weeks 5–7	Week 8	Weeks 9–11	Week 12
Total conditioning duration (min)	36	24	38	26	38	26
Net exercise time (min)	24	16	26	18	28	20
Net recovery time (min)	12	8	12	8	10	6
Work-to-rest ratio	~ 2:1	~ 2:1	~ 2.5:1	~ 2.5:1	~ 3:1	~ 3:1
Work interval (min)	6	4	6.5	4.5	7	5
Rest interval (min)	3	2	3	2	2.5	1.5
Number of exercises	16	16	16	16	16	16
Sets	4	4	4	4	4	4

Each HIFT session will begin with a 10-min warm-up consisting of low-intensity aerobic exercise, dynamic stretching, and movement preparation drills then end with a 5-min cool-down consisting of static stretching. Each HIFT session will consist of 4 sets of 4 functional exercises from the following categories in this order: (1) aerobic, (2) lower body strength, (3) upper body strength, and (4) abdominal/core strength. The exercises will be designed for translatability to various locations using minimal and portable equipment. The amount of load or resistance for each exercise will be determined on an individual basis according to the sRPE target stated above. One round will constitute performing a standardized amount of repetitions or seconds of each functional exercise, back-to-back, in the order listed above. Repetitions will be performed at a standardized tempo (1 s concentric phase/2 s eccentric phase) with proper form. Participants will complete as many rounds as possible (AMRAP) in the prescribed amount of time with recovery in between according to specific work-to-rest ratios. All sessions within a week will be standardized to ensure consistency in dose among the three groups. The total length of each session will be less than 60 min including the warm-up and cool-down. See Fig. 1 for an example of a phase 1 HIFT session. See Table 2 for the list of possible exercises within each category.

**Table 2 Tab2:** Example of HIFT exercises in each category

Aerobic	Lower body strength	Upper body strength	Abdominal/core strength
Jumping jacks	Goblet squat	TRX chest press	Plank
Skaters	Rear lunge	Push-up	Plank knee drives
High knees jog	Curtsy lunge	TRX row	Side plank
Fast feet with box	Box jumps	Push/press	Russian twist
Kickboxers	Squat jumps	Overhead press	Lateral bends
Butt kick jog	Deadlift	TRX bicep curl	Bicycle crunch
Burpees	Box step-ups	TRX chest fly	Hollow hold
Jump rope	Back/front squat	Triceps dips	Leg lifts
	Wall sit	TRX triceps press	Farmers carry
	TRX pistil squat	Lateral/front raise	TRX plank roll-out
	Jump tuck	Bent-over fly	Exercise ball crunches
		Bent-over row	Plank frog hops
		Negative push-ups	

